#### Secondary outcomes

The same procedure will be applied to secondary outcomes: number of heavy drinking days, maximum number of drinks on any day, SIP-2R score, and academic performance score.

In order to test the secondary hypothesis that participants who used a smartphone app targeting unhealthy alcohol use will have greater reductions in drinking compared to the no-intervention control condition, the analyses will be replicated in the subsample of participants who actively downloaded the application or completed the matching procedure in the control group. Thus, participants randomized to have access to the app and who will actively use it will be compared to those randomized to the no-intervention control condition who completed the matching procedure (entering a personalized code on a website). This analysis is equivalent to a per-protocol analysis.

Analyses will be performed at the completion of data collection. Subgroup analyses will be performed among participants reporting a high level of drinking and potential alcohol use disorder. In order to examine the potential for differences in the efficacy of the application among these participants, we will conduct secondary analyses in subgroups: in men we will conduct secondary analyses among those with baseline AUDIT score > 10 and AUDIT scores > 13 [23]: in women the cut-off points will be AUDIT scores > 6 (optimal sensitivity/specificity for *Diagnostic and statistical manual of mental disorders* (DSM-5) alcohol use disorder) and AUDIT scores > 11) [23].

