## Introduction

Unhealthy alcohol use is a leading cause of morbidity and mortality among young people, including among university students in whom unhealthy alcohol use is associated with academic impairment, damage to self and others, and institutional costs [45]. In Switzerland and worldwide, a significant proportion of the mortality among young people is attributed to alcohol [13, 35, 36]. Students frequently experience the consequences of unhealthy alcohol use and the consequences tend to increase over time, despite prevention efforts [27]. Students are therefore an appropriate target for secondary prevention interventions aiming at reducing unhealthy alcohol use [1].

**Table 1 Tab1:** Schedule of enrollment, intervention and assessment (SPIRIT flow diagram)

Smartphone-based secondary prevention intervention for students with unhealthy alcohol use: study protocol of a parallel group randomized controlled trial					
Study periods	Inclusion procedure	Baseline assessment	Follow up		
Time point (month)	0	0	3	6	12
Expected duration (minutes)	3	10	10	10	10
Inclusion criteria	x				
Patient Information and informed consent	x				
Demographics (questionnaire)	x	x			
Primary outcome variables (questionnaires)		x	x	x	x
Secondary outcome variables (questionnaires)		x	x	x	x
Other outcomes of interest (questionnaires)		x	x	x	x
Randomization		x			
Intervention group		Access granted to application			
Application usage data		For intervention group participants, throughout follow-up period			

A challenge for addressing unhealthy alcohol use is that few with unhealthy alcohol use actively seek treatment [18]. Information technology has the potential to reach large parts of the general population [19, 22]. Compared to face-to-face interventions, interventions using information technology have a greater reach, can be more easily implemented, and are more consistent [42]. Numerous electronic interventions using CD-ROM, computers, or the Internet have been developed and tested [31, 50]. Electronic screening and brief intervention are considered effective methods for reducing unhealthy alcohol use [49, 56].

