## Methods

### Research questions

The proposed trial will test the effectiveness of a proactive secondary prevention smartphone-based intervention (application) in a randomized controlled trial among students with unhealthy alcohol use. We will use a no-intervention control condition.

The main research question is: “Is providing access to a smartphone application to students with unhealthy alcohol use effective in reducing drinking (primary outcome), and negative alcohol-related consequences (secondary outcome) or poor academic performances (secondary outcome)?” In addition, as those randomized to receive access to the app will not necessarily use it, we will assess whether using the smartphone application is effective in decreasing drinking. Thus, the secondary research question is: “Is using a smartphone application targeting unhealthy alcohol use effective in reducing drinking?” (Table 1 and Additional file 1).

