#### Secondary hypothesis

Participants who used a smartphone app targeting unhealthy alcohol use will have greater reductions in drinking compared to the no-intervention control condition (i.e. participants randomized to have access to the app and who will actively use it will have greater reduction in drinking than control participants).

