Participants in the intervention group will receive a message containing an ID number. Participants will be asked to download the application and to unlock it using the ID number provided. This will validate the download and “unlock” an incentive. These procedures ensure that participants have a valid phone number, have downloaded the application, and are participating only once in the study. Control group participants will receive a message with an ID number that they will enter on the web to unlock an incentive*.*

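### The test of the app-use hypothesis compares two subsets selected after randomisation by different tasks, and treats one incentivised unlock as active use

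*Protocol article*

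**What the plan says.** The secondary question in Research questions is "Is using a smartphone application targeting unhealthy alcohol use effective in reducing drinking". The Secondary hypothesis section makes it a comparison: "participants randomized to have access to the app and who will actively use it will have greater reduction in drinking than control participants". The section on Secondary outcomes under Statistical analyses says how it is tested: "the analyses will be replicated in the subsample of participants who actively downloaded the application or completed the matching procedure in the control group". That section then describes the intervention subset as active users and calls the analysis equivalent to per-protocol.

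Recruitment procedure describes the two steps that define the subsets. In the intervention arm, "Participants will be asked to download the application and to unlock it using the ID number provided". The purpose of that step is given next: "This will validate the download and “unlock” an incentive". In the control arm, "Control group participants will receive a message with an ID number that they will enter on the web to unlock an incentive". Both steps follow randomisation, which takes place on completion of the baseline questionnaire. Controls are not given the app.

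Table 1 lists application usage data, collected "For intervention group participants, throughout follow-up period".

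**The concern.** Randomisation makes the two arms comparable as allocated. It does not make people who install an alcohol app in one arm comparable with people who type a code on a web page in the other. If the tasks attract different people, and the difference predicts how drinking changes, the comparison mixes an effect of the app with selection.

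The exposure tested is also not the one asked about. The question and the hypothesis concern use; the criterion is a download confirmed by one unlock that earns an incentive.

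The analysis is the stated test of a formal hypothesis about effectiveness, so its result is likely to be read as the effect of using the app. Selection could make a null app look helpful, or mask a real effect.

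**Working it through.** **Step 1: the sections side by side.**

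- Exposure: using (Research questions); actively using (Secondary hypothesis); accessing (Outcome measures); downloading, then equated with actively using (Secondary outcomes).
- Controls: all control participants (Secondary hypothesis); only those who completed code entry (Secondary outcomes).
- Task, intervention arm: install the app and enter an ID to unlock it. Task, control arm: enter an ID on a website. Each unlocks an incentive (Recruitment procedure).
- Timing: both tasks come after randomisation.
- Adjustment: the analyses are replicated, so the covariates are those of the main model, age and gender (Statistical analyses).

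So the hypothesis and its test differ in both exposure and comparator, and nothing stated makes the two subsets exchangeable.

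**Step 2: what could cause bias.** The main model has a subject random effect and a time-by-intervention term, and drinking is measured at baseline. If baseline is among the modelled times, a difference in drinking between the subsets that is the same at baseline and 6 months cancels from the interaction. Only selection linked to *change* in drinking then biases the result. Motivation to cut down could act in this way. Statistical analyses also describes a comparison of the groups at 6 months, so the exact contrast is not certain.

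**Step 3: an illustration of sensitivity, not an estimate.** The protocol gives no download rate, code-entry rate or strength of selection; all three are assumed here. The calculation is a simple two-group comparison with no true effect, not the planned count model. Let r be the correlation between the propensity to complete the step and lower values of the quantity compared, and p the completion proportion.

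- Bias = −r × [h(p_int) − h(p_ctrl)], where h(p) = φ(z)/p and z is the normal quantile cutting off the upper proportion p.
- Analysed per arm: 848 × 0.9 × p = 763.2 × p (848 per group and 10% attrition, from Sample size).
- SE = √(1/n_int + 1/n_ctrl), in SD units.
- For scale, 551 per group at 90% power and two-sided 5% implies (1.960 + 1.282) × √(2/551) = 0.195 SD, ignoring clustering.

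Worked case, r = 0.1, 60% download, 95% code entry: h(0.60) = 0.644 and h(0.95) = 0.109, so bias = −0.1 × 0.535 = −0.054 SD. With n = 458 and 725, SE = 0.060, and the chance of a false positive is about 15% instead of 5%.

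With code entry at 95%:

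| r | 80% download | 70% download | 60% download |
|---|---|---|---|
| 0.1 | −0.02 SD, 7% | −0.04 SD, 10% | −0.05 SD, 15% |
| 0.2 | −0.05 SD, 14% | −0.08 SD, 28% | −0.11 SD, 43% |
| 0.3 | −0.07 SD, 26% | −0.12 SD, 53% | −0.16 SD, 77% |

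(Each cell: bias, then two-sided type I error.)

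Two further cases show what the matching step can and cannot do. With equal completion rates and identical selection, bias is 0 and the error rate is 5%. With 75% completing in each arm but selection differing (r = 0.2 against 0), bias is −0.2 × 0.424 = −0.085 SD and the error rate is 30%. Equal completion rates alone therefore do not restore comparability.

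**Step 4: the alternative.** With controls having no app, the complier-average effect on an additive scale is about the intention-to-treat effect divided by the download proportion: 1.67, 1.33 and 1.11 times that effect at assumed proportions of 0.60, 0.75 and 0.90. Its SE on the same scale is √(2/763.2)/p = 0.051/p, which is 0.085 SD at 60% and 0.064 SD at 80%. The planned comparison has 0.060 and 0.055 SD, with code entry at 95%.

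**The case against.** The code-entry step is a deliberate attempt to mirror selection, and is probably better than comparing downloaders with all controls. Both arms earn an incentive, and the more the incentive drives installation, the weaker selection by motivation to drink less becomes. The analysis is secondary and labelled per-protocol, and Outcome measures speaks of association. All of this stands and limits the point. It does not show that the same kind of person completes both tasks, and Research questions still asks whether use is effective.

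Some stronger readings are tempting and not supported:

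- A reader might infer that someone who never opens the app counts as a user. The unlocking step requires at least one opening; the supportable complaint is that one unlock says little about active use.
- A reader might take a figure such as 0.05 SD or a 15% error rate as the bias of this trial. Those rest on assumed rates and correlations and on a simpler model without a baseline measure.
- A reader might infer that the bias must favour the app. That is plausible, but the protocol does not establish it.
- A reader might infer that the usage data will be ignored. They are collected; the article only does not use them to define the exposure here, and a fuller document may.

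The alternative has limits too. A simple instrumental-variable estimate rescales the intention-to-treat effect, so it gives an effect size for those who took up the app rather than much independent evidence. Fitting it with a count outcome and multiple imputation takes some work.

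**Conclusion.** The point holds. The test of the secondary hypothesis rests on two subsets formed after randomisation by different tasks, so it is a non-randomised comparison; code matching and adjustment for age and gender do not secure comparability. The exposure and the control group are worded inconsistently, and an incentivised unlock stands in for active use.

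The size and direction of bias are unknown. Under the assumptions above it runs from zero (equal rates, identical selection) to a large part of the 0.195 SD implied by the sample size; in the planned model, if the contrast is the time-by-intervention term, only selection linked to change in drinking would matter. The primary intention-to-treat analysis is untouched. This should be changed because the remedy is cheap and uses data already being collected.

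**What to change.** 1. Make the test of the secondary hypothesis a complier-average causal effect that keeps all randomised participants, with allocation as instrument and download/unlock as the main exposure. Non-compliance is one-sided because controls get no access. Use an estimator suited to count data, and state the exclusion restriction: allocation affects drinking only through download/unlock.
2. As a sensitivity analysis, fix in advance a stricter definition of use from the logged data. Note that its exclusion restriction is less credible, because the first session may already deliver content such as the personalised feedback.
3. Keep the download versus web-code comparison as a supportive per-protocol analysis, labelled non-randomised.
4. Use one term for the exposure and one definition of the control group across Research questions, Secondary hypothesis, Outcome measures and Secondary outcomes.

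Cost: wider confidence intervals, an added assumption to state and defend, and some extra analysis. No new data collection is needed.

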### Statistical analyses

The primary analysis will answer the main research question: “Is providing access to a smartphone app effective in reducing drinking compared to a no-intervention control condition?” The primary analysis will be to compare the intervention and control groups at 6 months on the primary outcome measure: the volume of alcohol drunk reported as the mean number of drinks per week over the past 30 days. All available data will be used in an intent-to-treat paradigm (i.e. individuals will be analyzed according to their initial group allocation). Missing values will be handled through a multiple imputation procedure in order to respect the intention-to-treat paradigm [28]. The null hypothesis is that both conditions have comparable effects on the volume of drinking at the 6-month follow up. The alternative hypothesis is that participants in the intervention group (experimental condition: secondary prevention intervention) will report a smaller volume of drinking at the 6-month follow up compared to participants in the control group.

Count models will be used. Because we are expecting that the data will not be normally distributed, an adequate count model will be selected by comparing different count models. From previous studies conducted with the same outcome, we expect a negative binomial regression model to best fit the distribution of the sample [5, 6]. If this is confirmed, the impact of the intervention will be assessed by a random-effects negative binomial model for mean number of drinks per week. The model will specify subject and recruitment site as random effects and intervention and time as fixed effects (with a time * intervention interaction term). The model will be adjusted for age and gender.

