### Sample size

The sample size computation is based on studies conducted in similar populations, testing the efficacy of electronic interventions. The sample size was computed for the primary analysis: evaluation of intervention effects at 6 months on the number of drinks per week (past 30 days). Considering results reported by our group on an Internet-based brief intervention study conducted in Switzerland [5, 6], the sample size required is 551 individuals per group to demonstrate a significant difference with power of 90% and α type I error of 5%. Considering the potential need to adjust for clustering (recruitment on four sites with hypothetical low intraclass correlation of rho = 0.001) and an attrition rate of 10%, 848 participants per group are needed (771 + 77). A total of 1696 individuals is therefore the minimum number to be included.

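### The subgroup plan aims to examine differences in efficacy among heavier drinkers but analyses only the subsets above AUDIT cut-offs, so it yields no estimate of a difference

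*Protocol article*

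**What the plan says.** All references are to the protocol article.

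- **Secondary outcomes, who is analysed:** "Subgroup analyses will be performed among participants reporting a high level of drinking and potential alcohol use disorder".
- **Secondary outcomes, purpose and method:** to "examine the potential for differences in the efficacy of the application among these participants, we will conduct secondary analyses in subgroups".
- **Secondary outcomes, cut-offs:** "in men we will conduct secondary analyses among those with baseline AUDIT score > 10 and AUDIT scores > 13"; "in women the cut-off points will be AUDIT scores > 6", with a second, higher cut-off of 11 for women. Within each sex the higher subset is nested in the lower one.
- **Statistical analyses, model:** a random-effects negative binomial model is expected, with "subject and recruitment site as random effects and intervention and time as fixed effects (with a time * intervention interaction term". Covariates: "The model will be adjusted for age and gender". Baseline AUDIT is not named as a model term.
- **Sample size:** computed for the whole-trial comparison at 6 months. It starts from 551 per group (90% power, 5% type I error) and rises to 771 and then 848 per group for clustering and attrition. No subgroup share or subgroup power is given.

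**The concern.** A difference in efficacy is a contrast between two effects: the effect above the cut-off and the effect below it. The stated method estimates only the first. No participants below the cut-offs enter the comparison, and the only interaction in the model is between time and intervention. The aim and the method stand in the same sentence and do not match. An analysis plan that implemented the sentence literally would carry the mismatch forward.

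The risk is misinterpretation in both directions. A non-significant subset result can arise simply because the subset is smaller than the trial. A significant one can arise when the app works equally well in everyone. Neither supports a statement that the app works worse, or better, in students with likely alcohol use disorder. Such a statement could matter when the app is disseminated.

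**Working it through.** **1. The plan's own figures.** The inputs are 551 per group, 90% power, 5% type I error, "recruitment on four sites with hypothetical low intraclass correlation of rho = 0.001", and 10% attrition (Sample size). Sidedness is not stated; two-sided is assumed.
- Design effect 1 + (m − 1) × 0.001. With m = 400 per site, 551 × 1.399 = 771. With m = 1542/4 = 385.5, 551 × 1.3845 = 763. Both agree with the stated 771 to about 1%.
- Attrition: 771 + 77 = 848, as stated. Dividing by 0.9 would give 857; the difference is immaterial here.
- The 551 cannot be re-derived, because no effect size or dispersion is given. Back-solved, it implies a standardised effect of (1.96 + 1.2816) × √(2/551) ≈ 0.195.

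**2. Power inside a subset when the effect is the same in everyone.** At 90% power the expected z-statistic for the whole trial is 1.96 + 1.2816 = 3.24. A subset holding a share f of participants has expected z = 3.24 × √f, and power ≈ Φ(3.24√f − 1.96). For example, at f = 0.30: 3.24 × 0.548 = 1.775, and Φ(1.775 − 1.96) = 0.43. The shares are assumptions.

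| Assumed share f | Power in subset, overall power 90% | Same, clustering inflation counted as information |
|---|---|---|
| 10% | 18% | 23% |
| 20% | 31% | 40% |
| 30% | 43% | 55% |
| 50% | 63% | 77% |
| 70% | 77% | 89% |

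The last column treats 763 completers per arm (848 × 0.9) as independent: Φ(0.1953 × √(763f/2) − 1.96). Overall power would then be 97%. The 90% column is the better guide, because the increase from 551 to 771 is there to offset clustering.

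In every row efficacy does not differ, so neither a significant nor a non-significant subset result says anything correct about a difference.

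**3. Analysing the complement separately is not enough.** If the groups below the cut-offs were also tested on their own, the two verdicts would disagree with probability a(1 − b) + b(1 − a), where a and b are the powers at f and 1 − f. At f = 0.30, a = 0.427 and b = 0.774, so 0.427 × 0.226 + 0.774 × 0.573 = 0.54. Over shares of 10% to 70% the range is 47% to 74%, again with no heterogeneity.

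**4. The interaction test.** Its standard error, relative to that of the overall effect, is √(1/f + 1/(1 − f)). It holds its false-positive rate at 5%. For shares of 10% to 70%, with 3.24 as the whole-trial z for the design effect:
- Effect in the subset double that in the rest, average held at the design effect: at f = 0.30, z = 3.24 × (1/1.3)/2.18 = 1.14, power 21%. Range 14% to 21%.
- Design effect in the subset, none in the rest: at f = 0.50, z = 3.24/2 = 1.62, power 37%. Range 16% to 37%.

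**The case against.** **Silence.** The article is condensed, and modelling details are commonly left to an analysis plan, which is not shown and could add an interaction term. That would answer a complaint about something merely left out. It does not answer this one, because the article states an aim and commits to a method that cannot meet it.

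**A milder aim.** Estimating the effect among likely cases of alcohol use disorder is legitimate in itself, and a subset estimate with its interval, set beside the whole-trial estimate, carries some information. Both points stand. But the stated purpose is to look at differences, and that needs a contrast.

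**Stronger readings that the article does not support:**
- A reader might infer that the plan will declare no effect in heavier drinkers in a stated fraction of trials. The article contains no rule for reading a subgroup result, so no such rate can be attributed to it.
- A reader might take the subsets to be small. Everyone enrolled has already screened positive on AUDIT-C (Participants), and nothing rules out a share well above 30% at the lower cut-offs. At 70% a null-looking result would occur in about 23% of trials.
- A reader might infer separate analyses in men and women. The cut-offs are sex-specific, but the text does not clearly say whether the sexes are pooled. Separate analyses would have less power than shown.

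**Approximation.** The calculation assumes equal information per participant. In a count model heavier drinkers may carry somewhat more, which would soften the loss without removing it.

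**Conclusion.** The point holds as a mismatch between aim and method. Analyses confined to participants above AUDIT cut-offs cannot show whether efficacy differs from that in the remaining participants, at any sample size.

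How misleading the results could look depends on assumptions: a two-sided 5% test, a uniform effect, 90% overall power and an unknown subset share. On that basis a null-looking subset would be expected in about 82% of trials at a 10% share, 37% at 50% and 23% at 70%. These figures illustrate the hazard; they do not predict what the investigators will conclude.

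The analyses are secondary and their cut-offs are pre-specified. The primary comparison, main hypothesis and sample size are unaffected. The wording should still be corrected, because a better method is available on data already being collected.

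**What to change.** Fit one model in all randomised participants with an intervention-by-baseline-AUDIT interaction on the 6-month contrast. Because the model already contains time by intervention, this means the matching terms with time as well. AUDIT may enter as continuous and centred by sex, or as one sex-specific above/below indicator per cut-off, pooling men and women.

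Report the ratio of rate ratios with its 95% CI, and the stratum-specific rate ratios from the same model. Base any statement about differing efficacy on the interaction estimate. Label the analysis exploratory, and state in advance that an inconclusive interaction will not be read as equal efficacy.

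**Cost:** a change of wording and one extra set of model terms; the imputation model should carry the same interaction. No new data are needed and the primary analysis does not change. The downside is the low power shown above, so the result may well be inconclusive.
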